**Secondary outcome measure: 1) number of complaints**

Complaints emanating from targeted wards (total and allied health specific) will be captured through the hospital administrative databases and local departmental datasets.

**Secondary outcome measure: 2) number of compliments**

Compliments emanating from targeted wards will be captured similarly to the number of complaints.

**Secondary outcome measure: 3) patient discharge destination**

Patient discharge destination will be classified into categories of: i) discharged to the community, ii) transferred to another acute ward, iii) transferred to intensive care, iv) transferred to rehabilitation, and v) discharged to residential aged care.

**Secondary outcome measure: 4) patient satisfaction**

Patient satisfaction with overall care will be measured using data from the 'overall hospital experience' domain of the Victorian Patient Satisfaction Survey [30]. These data will only be extracted from participant group 2

(randomly selected subgroup of patients from participating wards). These data will not be collected from patients with a diagnosis of dementia or cognitive impairment documented in their medical history.

**Secondary outcome measure: 5) patient functional independence at discharge**

Patient independence at discharge will be measured using participant self-report on the Modified Barthel Index [31]. These data will be collected from the same participant subgroup as secondary outcome measure: 4) patient satisfaction.

**Secondary outcome measure: 6) patient health-related quality of life at discharge**

Health-related quality of life at discharge from hospital will be measured using the European Quality of Life, 5 dimensions (EQ-5D-5 L) instrument [32]. These data will be collected from the same participant subgroup as secondary outcome measure: 4) patient satisfaction in study 2.

**Secondary outcome measure: 7) staff absenteeism**

Staff absenteeism (medical, nursing, allied health staff) will be collected through routine finance reporting. As allied health staff are not allocated to specific wards, but may work across a combination of wards with mixed exposure to intervention and control conditions, we will collect these data at only 3 time points: the first month of study 1, the final month of study 1 and the final month of study 2.

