**Table 1 Caseload in participating wards**

| Hospital           | Ward             | Description                                                         |
|--------------------|------------------|---------------------------------------------------------------------|
| Dandenong Hospital | SW3/W2 acute     | Orthopaedic surgery                                                 |
|                    | SW4              | Stroke unit                                                         |
|                    | West 3           | Thoracic, Vascular, General surgical and medical units              |
|                    | West 4           | General medicine                                                    |
|                    | North Ward       | Head and neck, Plastics                                             |
|                    | North 3          | Surgical                                                            |
| Western Hospital   | 2B               | Medical                                                             |
|                    | 2C               | Medical                                                             |
|                    | 2D               | Infectious diseases; Respiratory medicine                           |
|                    | 2 W a | Plastics; Head and neck surgery; ENT surgery                        |
|                    | 3 W              | General surgery; Colorectal; Breast; Endocrine; Urology             |
|                    | 3E               | General surgery; Vascular surgery; Thoracic; Upper gastrointestinal |

aStudy 1 only.

different time points (Dandenong Hospital commencing February 2014 and Western Hospital (Footscray) commencing April 2014).

Data in this study will be collected from three groups of participants. Each group of participants is now described in detail.

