#### **Group 1**

'All patients on participating wards.' This group will consist of patients admitted to acute medical or surgical wards involved in the trial who are over the age of 18 years. Paediatric patients will be excluded from this study as they are not routinely seen on the selected wards (none are paediatric units or have paediatric beds) and have different provisions for service delivery. It is anticipated, based on previous patient flow data, that each ward will have an average of 174 patient admissions per month during the trial. This means that 6 wards at 1 site will have 7,308 patient admissions during the 7 months of study 1 and 7,308 during the 7 months of study 2. This will lead to an anticipated total of 29,232 patient admissions during the overall study period.

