#### **Study 1 intervention condition - current weekend allied health services**

Current physiotherapy, occupational therapy, social work, dietetics, speech pathology and allied health assistant weekend service delivery on the participating wards will be the intervention for study 1 of this trial. During this study, the weekend allied health services of each participating ward (cluster) will be 'rolled in' sequentially using the stepped wedge design (Figure 1 and Additional file 1). The current model of weekend allied health service delivery in the hospitals participating in this study has not been developed systematically, rather in an '*ad hoc*' manner driven by decisions made by individual allied health managers. Thus, there is potential that this model is not currently tailored to the needs of individual wards and is, therefore, not delivering optimal outcomes. However, it is the prevailing model of care that in a pragmatic research design serves as an appropriate reference standard [23].

Design at Western Hospital (Footscray) is similar but with 5 wards involved in study 2 and a 13-month total study period. Black = current weekend allied health service. White = no weekend allied health service. Grey = new, stakeholder-driven weekend allied health service. Twelve months of pre-trial data collection at participating sites indicated that weekend allied health services at each site varied in terms of the number of disciplines involved, the amount of time allocated per ward and the total budgetary allocation to this activity. Steps will be taken during study 1 to ensure intervention fidelity relative to the pre-trial data collection. Allied health staff providing weekend services will be updated as to the amount of time spent on each ward per month and will have pre-trial data used as monthly targets to ensure that service provision levels within study 1 intervention periods are consistent with pre-trial data. Staff will be advised to continue performing tasks and prioritising patients in the same manner with which they had been doing so prior to trial commencement.

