Sensitivity analyses will be conducted if there are unit closures (for example, surgical unit closures over the Christmas holiday period) that are likely to affect the caseload on related wards at these times. Data within these cells of the stepped wedge design will be treated as missing in the sensitivity analyses.

**Economic analysis** The primary economic analysis will be a cost-effectiveness analysis from the hospital perspective that examines the incremental cost per patient admitted. These costs will include the 'total cost' of patients during their admission plus additional costs from an unplanned admission within 28 days. Data from patients who are transferred between wards in different study periods (that is one without access to allied health services, one with access to allied health services) will be excluded from the analyses as will data from patients who remain within the same ward over two or more weekends if they are allowed to access weekend allied health services during one weekend, and not allowed to access allied health services on another. Secondary economic evaluations will examine the incremental cost per difference in clinical outcome for the measures of functional independence (studies 1 and 2) and health-related quality of life (study 2).

**Qualitative data analysis** Both content and thematic analysis will be used for the analysis of qualitative data collected as a part of this study [38].

**Analysis of workforce absenteeism outcome** It was initially planned to analyse these data in a similar manner to other outcomes; however, it has become apparent that for some professional groups, staff operate over multiple wards that may be in the intervention or control periods during the study. Hence, we will only compare data collected from the first and last months of each study when all wards within the study are either completely in control or intervention periods.

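### Staff absenteeism is collected at three months but compared at four, and on either version the service effect cannot be separated from season

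*Protocol*

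**What the plan says.** Two places in the protocol fix how staff absenteeism is handled.

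- **Secondary outcome measure: 7) staff absenteeism.** Data on medical, nursing and allied health staff come from routine finance reporting. The section states "we will collect these data at only 3 time points: the first month of study 1, the final month of study 1", and names the final month of study 2 as the third point. The reason given is that allied health staff are not tied to single wards.
- **Analysis of workforce absenteeism outcome (under Statistical analysis).** "It was initially planned to analyse these data in a similar manner to other outcomes", but because some professional groups work over several wards, "we will only compare data collected from the first and last months of each study". These months are chosen as those "when all wards within the study are either completely in control or intervention periods".

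For the main outcomes, the Statistical analysis section adjusts for each step of the wedge and for two years of historical site data mapped to those steps, to deal with local seasonal variation. Neither absenteeism section says that this adjustment applies to absenteeism.

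**The concern.** The analysis rule calls for a month that the collection rule leaves out. Someone following the collection rule would reach the study 2 comparison without the baseline month that the analysis section names.

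The second issue remains whichever list is used. A stepped wedge separates the intervention from time because, in the middle months, some wards have the service while others do not. The absenteeism rule keeps only months in which that is never so, and the randomised order of the wards then contributes nothing to this outcome. Sick leave may well vary over the year, and the protocol itself expects seasonal variation in its outcomes. A seasonal change could therefore be reported as an effect on staff of withdrawing or restoring the service.

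**Working it through.** **1. Timeline inputs, checked against the plan's own figures.** The Group 1 section gives 174 admissions per ward per month and "7,308 patient admissions during the 7 months of study 1 and 7,308 during the 7 months of study 2". 174 × 6 wards × 7 months = 7,308, and 7,308 × 4 = 29,232; both match the text. Seven months is six wards plus one initial month. For Western Hospital the protocol states "5 wards involved in study 2 and a 13-month total study period": (6 + 1) + (5 + 1) = 13, which also matches.

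**2. Are the last month of study 1 and the first month of study 2 the same month?** If they were shared, Western's total would be 7 + 6 − 1 = 12, not 13. The section on the study 2 intervention has the first ward resuming service at the second step, so the first month of study 2 is a month of its own with no service on any ward.

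**3. Count of months.** Analysis section: 2 studies × 2 months = 4. Collection section: 3. The missing one is the first month of study 2.

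**4. Calendar.** Inputs: starts in February 2014 (Dandenong) and April 2014 (Western), monthly steps, and study 2 directly after study 1 (Design section).

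| Hospital | Study 1 first (current service) | Study 1 final (none) | Study 2 first (none) | Study 2 final (new model) |
|---|---|---|---|---|
| Dandenong | Feb 2014 | Aug 2014 | Sep 2014 | Mar 2015 |
| Western | Apr 2014 | Oct 2014 | Nov 2014 | Apr 2015 |

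The collection section omits the fourth column (Sep and Nov 2014). All service-on months lie in February to April and all service-off months in August to November, on the three-month or the four-month list. The on-off-on sequence does not cancel season, because both on readings come from the same part of the year.

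**5. Identifiability.** Take a model with ward, month and condition effects for six wards. With all seven months of study 1, condition adds 1 degree of freedom (rank of the design matrix) beyond ward and month. With only the first and last months it adds 0: every ward is on in the first and off in the last, so the condition column equals the indicator for the first month. For each contrast,

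expected (off − on) = service effect + (calendar effect of off month − calendar effect of on month),

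and the bracket cannot be estimated from these data.

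**6. Do the staggered hospitals help?** No compared calendar month has one hospital on and the other off. Data collection is planned to end in June 2015, two months after Western's April 2015, so gaps of one and two months between the studies were also tried. Study 2 then runs from Oct 2014 to Apr 2015 or Nov 2014 to May 2015 at Dandenong, and from Dec 2014 to May 2015 or Jan to Jun 2015 at Western. There is still no concurrent on/off pair. The February-April against August-November pattern itself belongs to the no-gap schedule that the protocol states.

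**The case against.** - **The study 2 contrast.** A reader might infer that it cannot be computed. That goes too far. The final month of study 1 adjoins the first month of study 2, the control condition is declared identical, and it could serve as the service-off reading. The source is a routine report, so the missing month could probably still be extracted. But no section says that the final month of study 1 is to be used. At Western it would also set a month with six wards against a study with five, since ward 2 W takes part in study 1 only.
- **The size of the bias.** A reader might infer a winter excess in sick leave of some definite size. The documents give no absenteeism level, seasonal pattern or expected effect. Only Dandenong has a winter reading (August), and under the analysis rule its study 2 baseline is September. Western has none. What holds at both hospitals is the tie between condition and calendar time, not a winter effect of known size.
- **Readings per condition.** It is tempting to say that there is one reading per condition. The four-month version has two service-off readings, and the on-off-on sequence gives some check on a steady trend, though not on season.
- **Seasonal adjustment may be in the statistical analysis plan.** That plan is not at hand, and the protocol does not rule out using historical data here. It would reduce the seasonal part of the problem. It would not supply a concurrent control, and adjustment for step is impossible when step and condition coincide.
- **The restriction is disclosed and reasoned.** This stands for staff who cross wards. The same rule is nevertheless applied to medical, nursing and allied health staff, while the stated reason covers only some groups. Whether the others are ward-based is not stated, so a ward-level analysis is possible only on that assumption.

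**Conclusion.** The mismatch is real: three months collected, four compared. The sections must be reconciled. On either version the comparison is an uncontrolled before-after contrast within hospital, with on months in February to April and off months in August to November, so the service effect cannot be separated from season. The seasonal difference carries over in full; its size and direction cannot be quantified from the documents.

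This rests on monthly steps from the stated start dates and on study 2 following without a gap. The design figure is not available, so Dandenong's 14 months is inferred as 7 + 7. The confounding of condition with calendar time does not depend on the gap. The consequence is limited to one secondary outcome, which enters neither the stopping rules, nor the power analysis, nor the stated economic analyses. It should be corrected, but it does not touch the primary conclusions.

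**What to change.** 1. Amend the collection section to include the first month of study 2, so that at least the four compared months are collected.
2. Extract the same calendar months for the two years before the trial from the finance reports, and compare the change in the trial with the historical change. This extends to absenteeism the seasonal adjustment already planned for the main outcomes. The reference years should end before the trial starts: March 2014 at Dandenong and April 2014 at Western already lie inside study 1.
3. Where the reports identify ward-based staff by ward and month (an assumption; nursing is a possible case), extract all study months and analyse ward-months with the stepped-wedge model used for the other outcomes.
4. For any group where step 3 is not possible, label the result an uncontrolled before-after comparison.

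The cost is a somewhat longer extract from an existing report and one more analysis. Step 2 removes only seasonal patterns that are stable from year to year; only step 3 brings back the randomised comparison.

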**Process measure: 1) allied health hours of service**

Number of occasions of allied health service provision to each patient on weekends and weekdays will be collected.

**Process measure: 2) clinical exceptions**

The frequency and reason for clinical exceptions taking place will be recorded by project research personnel.

**Process measure: 3) proportion of patients discharged on a Saturday or Sunday**

This outcome is a potential indicator of patient flow during the study. It is important to consider patient flow as a process measure to ensure that bed-block is not occurring on the weekend.

**Economic outcome measure: 1) cost of inpatient treatment per patient**

Hospital clinical costing data will be used to measure the costs attributed to each patient. If administrative data for a particular patient is unable to be extracted, costing based on the most recent National Weighted Activity Unit calculators [33] will be used. This will be based on the overall

patient admission, not just their time spent on a ward under an intervention or control condition.

### **Qualitative outcomes**

Group and individual interviews will be conducted with staff members from each ward and weekend allied health staff at 3 time points (pre-study 1, between study 1 and study 2, and post-study 2) to explore their satisfaction with and experiences of the different weekend allied health service delivery models being examined.

### **Procedure**

Approval to conduct this study has been obtained from the Monash Health Human Research Ethics Committee (EC00383 - representing Dandenong Hospital) and the Melbourne Health Human Research Ethics Committee (2013.283 - representing Western Hospital (Footscray)) and this trial has been registered with the Australian New Zealand Clinical Trials Registry (ACTRN12613001231730 (study 1) and ACTRN12613001361796 (study 2)). It is anticipated that data collection will commence in February 2014 and be completed in June 2015 with reports and publications finalised by June 2016. A multi-site project executive committee has been developed consisting of all project investigators. This executive committee has developed a project communications plan in consultation with representatives from the Victorian Government, Department of Health. Further pre-trial communications with relevant health services unions, local site clinicians, managers and executives will also be undertaken prior to trial commencement. Extensive staff engagement has been undertaken for this project at both study sites prior to trial commencement.

### **Randomisation and allocation concealment**

The order in which weekend allied health services will be rolled in and out from each participating ward will be determined at random by an investigator blinded to ward identity. One investigator will develop pseudonyms for each ward while another investigator blinded to the true identity of each pseudonym will use a random number generator in Microsoft Excel (Microsoft Corporation, Redmond, WA, USA) to allocate ward number locations to each pseudonym. The first investigator will then be able to reveal which pseudonym represented which ward.

### **Masking**

Research assistants collecting and entering data will not be blinded to the allocation of wards within the stepped wedge research designs. The randomly selected subgroup of patients from participating wards will not be informed of the purpose of the interview as being for the evaluation of a randomised controlled trial. However, we cannot say that all of these participants will be

blinded as to the intervention they were exposed to. Masking will be applied to the trial data analyst. Six mock codes representing different orders in which the wards may have progressed through the stepped wedge design (using a Latin Square approach) will be used to blind the statistician conducting the final quantitative analysis from the true identity of each ward and the time sequence in which each ward was randomised.

### **Trial safety**

The process of disinvestment in allied health services has the potential to be detrimental to patient safety and/or organisational outcomes. The checking of stopping rules and development of clinical exceptions will, therefore, be used to ensure safety. A stopping rule allows data to be monitored and the trial to be stopped if there is evidence of a lack of safety or efficacy associated with the intervention [34]. During study 1, interim analyses will be conducted monthly to ensure that patient outcomes have not dropped below a pre-specified non-inferiority margin. This margin represents the maximum amount of gain anticipated if the amount of resources being saved were to be reallocated to another purpose. Discussion groups with clinicians and project investigators initially determined that the non-inferiority margin should be 0.8 multiplied by the standard deviation of the targeted outcome. This is equivalent to 'Cohen's large effect size' [35]. However, review of the standard deviations for the outcomes that these stopping rules would be applied to revealed that these margins were too wide to be acceptable to the management of participating hospitals. As a result of these consultations, the following stopping rules were developed:

1. The 95% CI of the effect (difference between means) of having no weekend allied health services exceeding a 1-day increase in mean length of stay.
2. The 95% CI of the effect (difference between proportions) of having no weekend allied health services exceeding an absolute change of 0.02 (2%) in the outcomes of the proportion of patients who stay longer than their average inlier Australian Refined Diagnosis-Related Group (ARD-RG), the proportion of patients who experience one or more of the previously specified adverse events, or the proportion of patients who are unexpectedly readmitted within 28 days.

Management at each site also reserved the right to review other study data (for example, the proportion of patients discharged on the weekend) in determining whether the study should continue at each site. Interim analysis will be conducted during each month of study 1 and reported back to the project executive committee.

The project executive committee will then forward their recommendations along with blinded data to an independent data-monitoring committee at each site to make a determination as to whether the project should be ceased on the basis of the analysis conducted.

Data will be collected in an identifiable form to allow data linkage with other project datasets but will then be de-identified for storage and analysis once linkages have been made.

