#### **Primary outcome measure: 1) length of stay**

Mean overall length of stay per patient who is treated on one of the targeted wards will be used as the primary outcome. This measure is often used as an indicator of hospital efficiency [26]. Length of stay is the key overall driver of inpatient costs and is the most readily available outcome to enable stopping rules to be checked during study 1. However, overall mean length of stay is limited as an outcome for this project as: i) these data can be skewed by highly influential outliers, ii) length of stay of longer-stay patients will not be known until they are

discharged (thus interim analyses for non-inferiority to check stopping rules may underestimate mean length of stay) and iii) patient admission casemix profile may vary over the study period (for example, a study ward may start admitting more patients who typically stay longer). To account for these limitations, we will also examine the proportion of patients who stay longer than their Australian Refined Diagnosis-Related Group average 'in-liner' length of stay according to data published from the previous year [27].

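### The study 1 stopping rules do not say which 95% confidence limit must pass the margin, the two readings behave very differently, and the monthly looks use incomplete outcomes

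*Protocol*

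**What the plan says.** The Protocol, under Trial safety, gives two numbered stopping rules for study 1. The first is "The 95% CI of the effect (difference between means) of having no weekend allied health services exceeding a 1-day increase in mean length of stay". The second is "The 95% CI of the effect (difference between proportions) of having no weekend allied health services exceeding an absolute change of 0.02 (2" per cent), applied to three proportions: stay beyond the AR-DRG inlier average, any listed adverse event, and unplanned readmission within 28 days.

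The same section describes the purpose in two ways. A stopping rule allows "the trial to be stopped if there is evidence of a lack of safety or efficacy", and the monthly analyses are there "to ensure that patient outcomes have not dropped below a pre-specified non-inferiority margin". On timing it says "Interim analysis will be conducted during each month of study 1 and reported back to the project executive committee". That committee sends recommendations to an independent data-monitoring committee at each site, which decides.

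Under Statistical analysis, Study 1, the final non-inferiority conclusion requires the upper confidence limit to lie below the margin. That sentence is not linked to the stopping rules.

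Under Primary outcome measure 1, the Protocol notes that longer stays are unknown until discharge, "thus interim analyses for non-inferiority to check stopping rules may underestimate mean length of stay". It adds the AR-DRG proportion as a response to this and to two other limitations of mean stay.

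**The concern.** An interval can exceed a margin in two senses. If its upper limit is above the margin, harm of that size has not been excluded. If its lower limit is above, harm of that size has been shown. The phrase about evidence of a lack of safety fits the second. The phrase about outcomes not having dropped below a non-inferiority margin fits the first, as does the upper-limit criterion in the analysis section. Rule 1 speaks of an increase; rule 2 speaks only of a change.

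The site committees rely on these rules while a service is being withdrawn. Two committees could read the same interval and reach opposite conclusions on whether the criterion is met. Outcomes that are unfinished at the data cut make it harder still to know what a crossing, or its absence, means.

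**Working it through.** **Plan's own figures.** The Protocol gives no operating characteristics for the stopping rules. Its only related figures are the Table 3 powers, from the Hussey and Hughes variance. With six wards and seven steps, that formula returns the single-site 0.65 and 0.96 if 1,000 patients per ward-step are entered (7,000/7). It returns 0.16 and 0.33 to 0.36 with 7,000/(6 × 7) = 167. That is a separate matter; the check below uses the stated throughput of 174.

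**Inputs.** 174 admissions per ward per month, six wards per site, seven months (Group 1); monthly steps (Abstract), so one ward switches per month from month 2; rates 0.40, 0.10 and 0.10 and coefficient of variation 0.4 (Table 3); margin 0.02 and a 95% interval (Trial safety). Month 1 has no contrast, because every ward has the service.

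**Standard error.** With s² = p(1 − p)/174, τ² = (0.4p)², I = 6 wards and T months of data:

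Var = I·s²(s² + Tτ²) / [(IU − W)s² + (U² + ITU − TW − IV)τ²]

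U is the number of no-service ward-months, W the sum of squared column totals and V the sum of squared row totals.

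Month 2: U = W = V = 1, so Var = 1.2·s²(s² + 2τ²)/(s² + τ²).
- p = 0.40: s² = 0.24/174 = 0.001379, τ² = 0.0256, SE = 0.0568, half-width 11.1 points.
- p = 0.10: s² = 0.09/174 = 0.000517, τ² = 0.0016, SE = 0.0330, half-width 6.5 points.

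Month 7: U = 21, W = V = 91, so Var = 6·s²(s² + 7τ²)/(35s² + 140τ²), giving SE = 0.0203 and 0.0123.

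**Crossing probability at a single look.**
- Upper-limit reading, no true effect: 1 − Φ(0.02/SE − 1.96).
- Lower-limit reading, true harm +0.06: Φ((0.06 − 0.02)/SE − 1.96).

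| Look | Upper, p = 0.40 | Upper, p = 0.10 | Lower, p = 0.40 | Lower, p = 0.10 |
|---|---|---|---|---|
| Month 2 | 0.95 | 0.91 | 0.10 | 0.23 |
| Month 4 | 0.90 | 0.78 | 0.29 | 0.66 |
| Month 7 | 0.84 | 0.63 | 0.50 | 0.90 |

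At month 2, with the coefficient of variation run from 0 to 0.8, the upper-limit figures are 0.93 to 0.95 (p = 0.40) and 0.88 to 0.92 (p = 0.10). The lower-limit figures are 0.10 to 0.16 and 0.21 to 0.36.

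**Across looks** (simulation, 20,000 runs). At +0.06 in one outcome, the lower-limit reading has been met by month 7 with probability 0.61 (long stay) or 0.93 (a 10% outcome). With +0.06 in all three, assumed independent, it has been met with probability 0.46 at month 2 and 0.95 by month 4. With no effect, any of the three crosses by month 7 with probability about 0.03. Under the upper-limit reading with no effect, at least one of the three crosses at month 2 with probability above 0.99.

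**Readmission.** Assume even discharges over a 30-day month, a cut at month-end, no lag and uniform readmission timing. The visible share of the newest month's readmissions is the mean of min(30 − t, 28)/28 over t from 0 to 30, which is (392 + 56)/840 = 0.53. A lag of 28 days would raise it to 1. At month 2 the newest month holds all the no-service data, so a true +0.06 appears as about 0.53 × 0.06 = 0.032. The lower-limit crossing probability becomes Φ((0.032 − 0.02)/0.0330 − 1.96) ≈ 0.06, against 0.23 with complete data.

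**Length of stay.** No standard deviation is given, so the 1-day rule cannot be evaluated. As an illustration only, with an assumed SD of 4 to 12 days and intraclass correlation of 0.02, the month-2 upper-limit crossing with no effect runs from 0.38 to 0.89. The lower-limit crossing at +3 days runs from 0.995 down to 0.32.

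**The case against.** The strongest reply is that an interval exceeding a margin, in a paragraph that ties stopping to evidence of a lack of safety, most naturally means the whole interval lies beyond it. That reading is reasonable, but the same paragraph also ties the looks to a non-inferiority margin, and the only limit named anywhere is the upper one. The text does not settle it.

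Four stronger inferences are tempting, and the Protocol does not support them:
- That the upper-limit reading stops the trial. A crossing goes through the executive committee to a site data-monitoring committee, which decides.
- That the lower-limit reading rarely detects harm of three times the margin. This describes the early looks at a single binary outcome. Detection is substantial by month 7, although all six wards have lost the service by then.
- That an improvement could trigger rule 2. Absolute most naturally contrasts with relative, and the surrounding paragraph is about harm. The missing direction is a point of wording.
- That incomplete stays are ignored. The Protocol discloses the problem and puts the AR-DRG proportion into rule 2. This helps in part: someone still in hospital may already be past the threshold, but the Protocol does not say that current inpatients are counted. It does nothing for readmission.

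It is also fair to say that data-cut handling may sit in an analysis plan or charter not at hand, so the 53% is conditional. The missing limit is different, because the Protocol itself sets out the numbered rules.

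**Conclusion.** The point holds as an ambiguity with large consequences. Per binary outcome at one site, the upper-limit reading is met at month 2 with probability 0.91 to 0.95 under no effect, and still 0.63 to 0.84 at month 7. The lower-limit reading is met at month 2 with probability 0.10 to 0.23 at a true +0.06, and about 0.50 to 0.90 at month 7. These figures assume 174 admissions per ward-month, the Table 3 rates and coefficient of variation, ward and step effects, and complete outcomes. The readmission loss, about half at the first look, depends on the stated timing assumptions. Nothing firm can be said about the length-of-stay rule without an SD.

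**What to change.** Reconcile the passages under Trial safety, and their relation to the upper-limit criterion under Statistical analysis, by naming one confidence limit and the harm direction in both rules. The lower limit of (no service minus service) is the one consistent with the phrase on evidence of a lack of safety. If that limit is chosen, the committees should be told plainly how low its early sensitivity is. Give them the crossing probabilities month by month under no effect and under stated harms, adding the length-of-stay rule once an SD from the pre-trial data is entered.

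At interims, analyse readmission as time to event censored at the data cut, or restrict it to discharges with 28 days elapsed. Analyse length of stay by admission cohort, with current inpatients kept as censored.

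Pooling the sites is no remedy at the first look: they start in February and April 2014, so the second site has no data at the first site's month-2 look.

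The cost is a wording change to the Protocol or monitoring charter and modest interim programming. The restriction to 28 elapsed days would also delay the readmission signal by about one look.
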